### Secondary endpoints

We expect that the data are not normally distributed due to the low number of participants. No statistical test will be used to compare the secondary endpoints in the two groups due to the lack of power. The results will therefore be descriptively presented.

### Questionnaires

#### GIQLI

The total sum score and the score for each item of the questionnaire for the intervention and control group will be presented as continuous numerical variables for both the 10th and 30th postoperative day, as depicted in Table 2.

| GIQLI             | 10 th postoperative day |                          | 30 th postoperative day |                          |
|-------------------|------------------------------------|--------------------------|------------------------------------|--------------------------|
|                   | Intervention group (n=x)           | Intervention group (n=x) | Intervention group (n=x)           | Intervention group (n=x) |
| Total      | x (x-x)                            | x (x-x)                  | x (x-x)                            | x (x-x)                  |
| Symptoms          | x (x-x)                            | x (x-x)                  | x (x-x)                            | x (x-x)                  |
| Emotions          | x (x-x)                            | x (x-x)                  | x (x-x)                            | x (x-x)                  |
| Physical function | x (x-x)                            | x (x-x)                  | x (x-x)                            | x (x-x)                  |
| Social function   | x (x-x)                            | x (x-x)                  | x (x-x)                            | x (x-x)                  |
| Medical treatment | x (x-x)                            | x (x-x)                  | x (x-x)                            | x (x-x)                  |

*Table 2. The median (range) scores of the Gastrointestinal Quality of Life Index (GIQLI) [3] overall and for each item of the intervention and the control group postoperatively.*

### Harms

The answers from the questionnaire regarding harms will be reported descriptively for the two groups the intervention and the control group in the Results section of the manuscript. Harms that were present will reported as the number and proportion in % in each group.

### ***Complications***

The data on complications will be presented as a dichotomous variable, where the number of complications and proportion in % are presented for each group, as depicted in Table 3.

Furthermore, deep surgical site infection, intraabdominal abscess, readmission and reoperations will be presented as dichotomous variables (with number and proportion in %) as depicted in Table 3 whereas Clavien-Dindo grading will be described in the text.

| Complications         | Intervention group (n=x) | Control group (n=x) |
|------------------------------|---------------------------------|----------------------------|
| Overall complications        | n (%)                           | n (%)                      |
| Deep surgical site infection | n (%)                           | n (%)                      |
| Intraabdominal abscess       | n (%)                           | n (%)                      |
| Readmissions                 | n (%)                           | n (%)                      |
| Reoperations                 | n (%)                           | n (%)                      |

*Table 3. The number and proportion in per cent of complications in the intervention and the control group.*

### ***Convalescence***

#### Time to return to normal activities

The time to return to normal activities in days will be presented both as dichotomous and continuous numerical variables in the Results section of the manuscript. The number and proportion in % of participants, who had returned within the 30th postoperative day, will be described. Dates for return will be used to calculate the continuous numerical variables. We expect that the data are not normally distributed due to the low number of participants, thus, medians and ranges for the intervention and control groups will be presented.

#### Period of sick leave

The period of sick leave in days will be presented both as dichotomous and continuous numerical variables in the Results section of the manuscript. The number and proportion in % of participants, who were still on sick leave at the 30th postoperative day, will be described. Dates for return from sick leave will be used to calculate the continuous numerical variables.

We expect that the data are not normally distributed due to the low number of participants, thus, medians and ranges for the intervention and control groups will be presented.

### ***Adverse events***

Adverse events and serious adverse events will be presented as dichotomous variables, where the number of complications and proportion in % are presented for each group in the Results section of the manuscript, furthermore, details on the adverse events will be described.

### **Missing data**

Missing data regarding the primary outcome, length of stay, will be excluded from the analysis as total length of stay was defined from the end of surgery until 30 days postoperatively.

Missing data in the secondary outcomes regarding the questionnaires (GIQLI and harms) will be treated as follows. All received GIQLI questionnaires regardless of the amount of missing data will be included. If the questionnaire was never received data will be excluded. All received questionnaires regarding harms will be reported regardless of missing data.

Missing data of the secondary outcomes complication and adverse events due to lack of 30th day contact with participant cannot be reported. If no dates have been registered for the secondary outcomes of convalescence the data are excluded from the calculations of the continuous numerical variables.

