### Secondary outcomes

#### *Questionnaires*

##### Gastrointestinal Quality of Life Index (GIQLI)

A disease-specific questionnaire [3] validated in Danish [4] was collected at 10 days postoperatively ( $\pm 2$  day) and at 30 days postoperatively ( $\pm 3$  days). The questionnaire evaluates the quality of life after surgery. It contains 36 questions, which explores five main domains: symptoms (19 items), physical status (seven items), emotions (five items), social functioning (four items), and the effect of medical treatment (one item). A five-point Likert-scale (0–4 points) is used to answer all items. The scale ranges from “never” to “all the time”. A higher score denotes a better function.

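### GIQLI sum scores admit every returned form however incomplete, with no item-level scoring rule; summed plainly, each blank counts as the worst answer

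*SAP*

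**What the plan says.** The outcome description (SAP, Secondary outcomes, GIQLI) says of the instrument: "It contains 36 questions, which explores five main domains". The domain counts are 19 for symptoms, seven for physical status, five for emotions, four for social functioning and one for medical treatment. On scoring it says "A five-point Likert-scale (0–4 points) is used to answer all items" and "A higher score denotes a better function".

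The analysis section (SAP, Secondary endpoints, GIQLI) will present "The total sum score and the score for each item of the questionnaire" at days 10 and 30. The rows of Table 2 are the total and the five domains, so the word item there means domain. Each cell is a median with range, and there is one n per column.

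The Missing data section separates forms that came back from forms that did not. For the first, "All received GIQLI questionnaires regardless of the amount of missing data will be included". For the second, "If the questionnaire was never received data will be excluded". Neither that section nor Statistical methods says how a returned form with unanswered items is turned into a score.

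**The concern.** A sum score has a defined value only if every item is answered or a rule says what replaces a blank. The SAP admits all returned forms and removes any completeness requirement, but supplies no such rule. The most direct way to carry this out is to add up whatever was answered. Because 0 is the bottom of the item scale, that treats a skipped question as the poorest possible function.

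The reported medians and ranges would then mix poor function with incomplete answering. GIQLI will only be described, so these values are all that a reader gets for this outcome. With one n per column in Table 2, a reader could not tell which values come from incomplete forms.

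**Working it through.** **Inputs from the SAP.** Domain counts 19, 7, 5, 4 and 1; item range 0 to 4, higher better; six patients planned per group (Sample size); median and range as the summary (Table 2).

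**Inputs assumed.** The SAP gives no expected item mean and no rate of missing items. I take a mean of answered items m from 2 to 3.5, and k blanks per form.

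**Scale check.** 19 + 7 + 5 + 4 + 1 = 36 items, which agrees with the SAP. The maximum total is 36 × 4 = 144.

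**Shortfall per form.** A plain sum gives (36 − k) × m. The prorated total is 36 × m. The difference is k × m.

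| m | prorated total | k = 1 | k = 4 | k = 9 | k = 18 |
|---|---|---|---|---|---|
| 2 | 72 | 2 | 8 | 18 | 36 |
| 2.5 | 90 | 2.5 | 10 | 22.5 | 45 |
| 3 | 108 | 3 | 12 | 27 | 54 |
| 3.5 | 126 | 3.5 | 14 | 31.5 | 63 |

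The entries under k are points lost. At m = 3 with half the form blank, the plain sum is 18 × 3 = 54 against 108. The comparison is with the prorated value; the true complete total is unknown. Whatever the blanks would have been, the plain sum cannot exceed the complete total, and its ceiling falls by 4 per blank (27 × 4 = 108 instead of 144 for k = 9).

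**Domains.** One blank can cost up to 4 of 4 × 4 = 16 points in social functioning, and the whole 4-point scale in the one-item medical treatment domain.

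**Effect on a group of six (illustrative totals).** Take complete totals of 90, 98, 104, 110, 116 and 122. The median is (104 + 110)/2 = 107. A form with 9 blanks keeps 27/36 = 0.75 of its total.

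- The form at 110 is affected: it becomes 82.5. The ordered values are 82.5, 90, 98, 104, 116, 122, so the median is 101 and the minimum falls from 90 to 82.5.
- The forms at 104 and 110 are both affected: they become 78 and 82.5. The median is (90 + 98)/2 = 94 and the minimum is 78.
- The form at 90 is affected: it becomes 67.5. The median stays at 107 and only the minimum changes.

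**If the analyst prorates instead.** The downward pull goes, but there is still no floor on completeness. A form with a single item answered at 4 would give 36 × 4 = 144, and one answered at 0 would give 0. Both would be admitted as the rule stands.

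**The case against.** The strongest objection is that the Missing data rule says only which forms enter the data set. A reader might infer that the SAP orders blanks to be scored 0. It does not say so anywhere. An analyst could include every form and prorate, or include it and report only the domains that are complete, and neither would produce the downward pull. The protocol or the cited instrument papers may also carry a convention for missing items, which cannot be checked here.

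This stands in part. Scoring blanks as 0 is the consequence of a plain sum, not a stated instruction. But the SAP sets out its own treatment of missing questionnaire data, refers to no convention elsewhere and removes any completeness threshold. Prorating is not mentioned, and without a minimum it would turn a near-empty form into a total. Setting a total to missing whenever an item is blank fits poorly with including every form. The same returned form can therefore yield different scores depending on how the sum is coded.

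Two further objections stand in full. GIQLI is a secondary outcome that the SAP will describe without testing, so the primary analysis of length of stay is untouched. And the numbers of blanks and the item means above are assumptions; nothing in the SAP suggests that half-empty forms are expected.

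**Conclusion.** The point holds as a defect in how the GIQLI score is fixed: all forms are admitted, a sum is reported, and nothing prevents a blank from counting as the worst answer. Under a plain sum, and for m between 2 and 3.5, the loss is 8 to 14 points for 4 blanks and 18 to 31.5 for 9 blanks, out of 144. In the illustrative group of six, one form with 9 blanks moves the median by 6 points, or only the minimum if it was already the lowest.

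A reader might go further and infer that the quality-of-life comparison is biased in favour of one group. The SAP does not support that. The downward pull is on each group's level, and a systematic difference needs item non-response to differ between the groups, on which the document is silent. With about six forms per group, a chance imbalance of one or two incomplete forms is still enough to disturb the published figures.

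**What to change.** Add this to the Missing data section for GIQLI, in place of the unconditional inclusion of received forms:

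> A multi-item domain score is calculated when at least half of its items are answered, as the number of items in the domain times the mean of the answered items; otherwise it is missing. The one-item medical treatment domain is reported only when answered. The total is calculated as 36 times the mean of all answered items when at least half of the items in each of the four multi-item domains are answered; otherwise it is missing. The number of forms contributing to each score and the number of missing items per form are reported.

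The total is tied to each multi-item domain so that it cannot be formed while one of them is nearly empty. The minimum is 10 of 19, 4 of 7, 3 of 5 and 2 of 4 items. A blank medical treatment item, which has no domain mean to draw on, does not block the total. The half-answered threshold is a workable convention, not one taken from the SAP; what matters is that a rule is fixed in advance and does not score blanks as 0.

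The cost is a few lines of SAP text and code, plus an n for each row of Table 2. The downside is that mostly empty forms drop out of the total. On an incomplete form the total also need not equal the sum of the prorated domain scores, which a table footnote can state.

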### ***Convalescence***

#### Time to return to normal activities

Time to return to normal activities: This time point was determined either 10 days ( $\pm 2$  days) postoperatively when the patients had their sutures removed by the trial personnel or 30

days ( $\pm 3$  days) postoperatively through the planned telephone interview of the participants. The date was defined at the time point at which the participant could return to normal daily activities.

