#### Period of sick leave

Period of sick leave (absence from work): This time point was determined either 10 days ( $\pm 2$  days) postoperatively when the patients had their sutures removed by the trial personnel or 30 days ( $\pm 3$  days) postoperatively through the planned telephone interview of the participants. The parameter was defined as the number of days from the operation to the time point at where the participant returned to work or school.

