#### **Sample size**

The power calculation for the trial was as follows. The cumulative 30-day length of stay was expected to be 72 hours with a standard deviation of 12 hours in the control group. When  $\alpha$  was set at 0.05,  $\beta$  was set at 0.80, and an acceptable difference between the groups was set at 48 hours, a randomised design requires 4 patients in each group, a total of 8 patients. However, as we expected data not to be normally distributed and planned to use a quasi-randomised design [8,9], we decided to include 6 patients in each group, a total of 12 patients to ensure sufficient power.

A participant has concluded the trial when the 30-day postoperative follow-up has been conducted. Inclusion of participants in the trial will continue until a minimum of six participants in each study group have reached the 30-day follow-up with data for the primary outcome parameter, total length of stay. Thus, we planned to include six patients in each study group and only if the primary outcome was not available at 30-day follow-up, further patients were included to ensure data on the primary outcome on six patients in each group.

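### Convalescence medians and ranges drop anyone without a return date, so any participant known not to have returned by the day-30 contact is left out and recovery looks faster

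*SAP*

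**What the plan says.** Both convalescence outcomes are times to a return. For normal activities the SAP (Outcomes, Time to return to normal activities) says: "The date was defined at the time point at which the participant could return to normal daily activities". Sick leave (Outcomes, Period of sick leave) is "the number of days from the operation to the time point at where the participant returned to work or school". Status is obtained at the day-10 visit or the day-30 telephone interview, and under Sample size "A participant has concluded the trial when the 30-day postoperative follow-up has been conducted". The SAP describes no later contact.

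Under Endpoints, Convalescence, time to normal activities "will be presented both as dichotomous and continuous numerical variables in the Results section of the manuscript", and sick leave is handled in the same way. The continuous part is built from dates alone: "Dates for return will be used to calculate the continuous numerical variables" for activities and "Dates for return from sick leave will be used to calculate the continuous numerical variables" for sick leave, each summarised by median and range per group. The dichotomous part gives the number and percentage who had returned to activities by day 30 and, for sick leave, the number and percentage of "participants, who were still on sick leave at the" same time point.

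The Missing data section then adds: "If no dates have been registered for the secondary outcomes of convalescence the data are excluded from the calculations of the continuous numerical variables". It makes no exception for participants known not to have returned. No censoring rule, >30 days category or time-to-event method appears in the SAP.

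**The concern.** A participant who tells the interviewer at day 30 that they are not yet back at work has no return date to register. Their recovery time is still partly known: it is longer than the time to that contact. The rule treats this person in the same way as someone who could not be reached. Known non-returners are the slowest recoveries in the group, so the exclusion is informative and acts in one direction only.

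At stake is how two patient-relevant secondary outcomes read. With about six participants per group, one or two exclusions visibly move a median. The group with more non-returners is flattered more. The range would also end at the slowest dated return although somebody in the group took longer.

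**Working it through.** **Inputs.** From the SAP: 6 participants per group (Sample size); median and range as the summary (Endpoints, Convalescence); exclusion when no date exists (Missing data). Not in the SAP: any expected recovery time or share not returned by day 30. All return times below are therefore assumptions, and there is no figure of the plan to reproduce.

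**Step 1: one group of six.** Assume return days 7, 10, 14, 18, 22, 26, and replace the slowest k by not returned at the day-30 contact. The SAP rule takes the median of the 6 − k dated values. The alternative keeps all six and ranks the k as >30.

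| k | Median, SAP rule | Median, all six kept | Maximum, SAP rule | Maximum, all kept |
|---|---|---|---|---|
| 0 | (14+18)/2 = 16 | 16 | 26 | 26 |
| 1 | 14 | (14+18)/2 = 16 | 22 | >30 |
| 2 | (10+14)/2 = 12 | (14+18)/2 = 16 | 18 | >30 |
| 3 | 10 | not determined (14 to >30) | 14 | >30 |
| 4 | (7+10)/2 = 8.5 | >30 | 10 | >30 |

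In this example the reported median falls as more participants fail to return.

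**Step 2: general form.** If a share p is removed from the upper tail, the reported median is, in large samples, the (1 − p)/2 quantile of all participants. For p = 1/6 this is (5/6)/2 = 41.7%; for p = 1/3, 33.3%; for p = 1/2, 25%. It is the 50th percentile only when p = 0.

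**Step 3: range of assumptions.** Simulated groups of 6 with lognormal times (100,000 groups per row). The reported median drops values above 30; the comparison median sets them to 31. Share beyond day 30 = 1 − Φ(ln(30/median)/log-SD).

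| Assumed median, log-SD | Beyond day 30 | Mean median, SAP rule | Mean median, all kept | Difference (days) |
|---|---|---|---|---|
| 10, 0.5 | 1% | 10.2 | 10.4 | 0.1 |
| 7, 0.7 | 2% | 7.3 | 7.5 | 0.2 |
| 10, 0.7 | 6% | 10.0 | 10.7 | 0.7 |
| 14, 0.5 | 6% | 13.8 | 14.5 | 0.7 |
| 14, 0.7 | 14% | 12.9 | 15.0 | 2.1 |
| 21, 0.7 | 30% | 16.2 | 21.5 | 5.2 |

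Differences are taken before rounding. The top rows are small largely because most groups have no non-returner: with 1.4% beyond day 30, the chance of at least one in six is 1 − 0.986⁶ = 8%; with 30.5% it is 1 − 0.695⁶ = 89%.

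**Step 4: can the order of two groups reverse?** Assume group A returns on days 7, 10, 12, 14, 18, 21, with median (12+14)/2 = 13. Group B returns on days 7, 10, 12, with three not returned. The SAP rule reports 10 for B, so B looks faster. With B's three ranked as >30, the midpoint median lies above (12+30)/2 = 21, so B is slower. By Kaplan-Meier, B's curve sits at exactly 0.5 from day 12 onward. If the median is the first time the curve is at or below 0.5, it is 12 for B and also 12 for A, a tie; otherwise B's median is not determined. A reversal relative to the ranked median is therefore possible, but this example depends on the convention.

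**The case against.** Four points on the other side have weight.

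- **Non-returners are not hidden.** The exclusion applies only to the continuous variables, and the SAP also reports the day-30 proportions. In Step 4, group B would appear as 3 of 6 (50%) returned with median 10, beside group A with 6 of 6 (100%) and median 13. A careful reader would see the problem. This stands, and it limits the consequence. It does not correct the median or range, which the SAP does not label as applying to returners only.
- **No inference depends on it.** The SAP plans no tests for secondary endpoints, and the primary outcome, length of stay, does not use these dates. This stands.
- **The size is unknown.** Planning to count those still on sick leave allows for a count of zero, and the bias is then zero. This stands, so the point is conditional.
- **Some exclusions are reasonable.** Participants with unknown status, or with no work or school to return to, cannot contribute a time. This stands too; the defect is only that known non-returners are not separated from them.

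A reader might infer more: that slow recoveries will certainly be removed, that the slower group will come out as the faster one, or that the trial's conclusion is affected. The SAP supports none of these. It gives no non-return rate, it keeps the proportions, and it bases no test on these outcomes.

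**Conclusion.** The concern holds in a limited form. Followed as written, the rule discards known information on anyone not back by the day-30 contact. With at least one such participant, the maximum is understated and the median can only stay the same or move towards faster recovery. The average effect on the median is about 0.1 to 0.2 day if 1 to 2% have not returned and about 5 days if 30% have not; these figures rest on assumed lognormal times in groups of 6, and the SAP does not show which case applies. The damage is confined to the medians and ranges of two descriptive secondary outcomes. It is worth correcting because the correction is nearly free.

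**What to change.** Replace the convalescence sentence under Missing data with a rule on these lines:

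- Participants known at the day-30 contact not to have returned stay in the calculation, ranked as >30 days (censored at last contact, since the contact window is ±3 days).
- Report the median on that ranking, as >30 or not determined where it falls there, and the range as x to >30. A Kaplan-Meier median is an alternative if its convention for a curve lying at exactly 0.5 is stated.
- Exclude only participants whose status is unknown or, for sick leave, who have no work or school to return to. Report their number per group.

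The cost is one SAP sentence and a matching note in the two Convalescence paragraphs. The day-30 proportions already require the status information, so no new data are needed.
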